**Objective:**

The principal aim of this study is to evaluate the efficacy and safety of SCRM in patients diagnosed with AJS.

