**Methods:**

This study is a prospective randomized controlled clinical trial that will be conducted at a single center and that has a follow-up period of 24 weeks. A total of 96 patients diagnosed with AJS will be recruited from outpatient and inpatient clinics at Shanghai Baoshan Hospital of Integrated Traditional Chinese and Western Medicine. These patients will be randomly assigned to either the experimental group (SCRM) or the comparison group (basic cervical manipulation [BCM]). Treatment sessions consisting of SCRM or BCM will be administered twice a week for a duration of 4 weeks. Clinical monitoring indicators include the presence or absence of clinical symptoms as recorded on a symptom recording form, cervical imaging examination findings using cervical computed tomography, degree of neck pain measured by a visual analog scale (VAS), cervical range of motion assessed through cervical mobility measurement, degree of vertigo evaluated using the Vertigo Symptoms Scale-Chinese Version (VSS-C), and adverse events that may occur during the follow-up period. The time points for data collection and follow-up are baseline and postintervention (weeks 4, 8, 12, 16, 20, and 24).

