**Conclusions:**

This investigation will yield dependable evidence regarding the efficacy and safety of SCRM in patients with AJS.

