### Sample Size

The sample size calculation is based on our previous clinical research in patients with cervical spondylosis of the nerve root type, using the same primary outcome instrument. The efficiency of SCRM is 89.5%, while that of BCM is 54.6%. The sample size calculation formula is as follows:

The α is .05 and 1–β is .90. According to estimations, 48 participants per group are needed considering that this is a long-term follow-up that is expected to have a dropout rate of no greater than 20%.

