### BCM Technique

The BCM technique does not differ depending on the type of AJS. The SOP of BCM for patients with AJS (all types) is as follows [18]. First, the patient assumes a seated position, and the manipulation therapist stands behind the patient’s left side. Second, the therapist manipulates the patient’s jaw by flexing their left elbow and applies pressure to the occipital area with their right hand, which is supporting the occipital bone with the right palm and supporting the other 4 fingers. Third, the therapist gradually rotates the patient’s head to the left until reaching the active limit position and then instructs the patient to relax their neck while continuing to rotate the head to the passive limit position using both hands. During this process, a momentary force is exerted to further facilitate the left rotation of the patient’s head, resulting in audible clicking sounds emanating from the neck. Fourth, the therapist performs the 3 steps on the right side of the patient. It is important to note that the therapist can freely select one side (left or right) of the patient for the procedure.

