### Statistical Analysis

The main objective of this study is to evaluate the clinical effectiveness of SCRM therapy in patients with AJS. Additionally, secondary analyses will be conducted to assess changes in VAS scores, VSS-C scores, imaging findings, and cervical mobility before and after treatment in patients with AJS. Analyses will be performed using IBM SPSS 22.0. The measurement data will be expressed using mean differences (mean and standard deviation). The repeated measurement data will be analyzed using within-group variance analysis. Enumeration data will be presented as rates. The sample size needed for the Pearson chi-square test to compare rates between the 2 groups before and after treatment will be determined using the normal approximation algorithm and a 1-sided test. This study employs the superiority test that uses a 1-sided test level of α=.05. A *P* value of ≤.05 signifies the rejection of H0, thereby establishing the superiority of the SCRM group over the BCM group. Conversely, a *P* value >.05 indicates that a definitive conclusion regarding superiority cannot be drawn at this stage. The safety analysis will employ the chi-square test to compare the incidence of adverse reactions between the 2 groups. In instances where the data fail to meet the requirements of the chi-square test, the Fisher exact probability method will be employed.

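### The stated safety test, at a sample size set for efficacy and against another rotational manipulation, cannot support the dependable evidence on safety that the article promises

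*Protocol article*

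**What the plan says.** The Abstract's Objective puts safety beside efficacy: "The principal aim of this study is to evaluate the efficacy and safety of SCRM in patients diagnosed with AJS". The Abstract's Conclusions state without condition: "This investigation will yield dependable evidence regarding the efficacy and safety of SCRM in patients with AJS". The Discussion (Findings and Strengths) repeats the promise, there conditional on the study succeeding.

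Statistical Analysis gives one inferential method for safety: "The safety analysis will employ the chi-square test to compare the incidence of adverse reactions between the 2 groups". Where the chi-square requirements are not met, "the Fisher exact probability method will be employed". No sidedness is given for this test. The one-sided .05 level in the same section belongs to the superiority test.

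Sample Size takes response rates of 89.5% (SCRM) and 54.6% (BCM), α .05, power .90 and dropout of at most 20%, and concludes that "48 participants per group are needed considering that this is a long-term follow-up". No adverse-reaction rate enters the calculation.

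The comparator is also a thrust manipulation. In BCM Technique, "a momentary force is exerted to further facilitate the left rotation of the patient’s head, resulting in audible clicking sounds emanating from the neck".

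Two other safety provisions count in the plan's favour. Statistical Analysis says that count data will be shown as rates. Adverse Events plans a judgement of severity and a five-level grading of relatedness for every event.

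**The concern.** A claim that a treatment is safe needs an upper limit on its risk. A test of equal incidence gives none. If it is significant, it shows that the arms differ. If it is not, it leaves open anything from no excess to a large one, and at this sample size non-significance is the likely result even when a moderate excess is real.

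The choice of comparator adds a second gap that depends on no assumed rate. Both arms receive a rotational thrust, so harm common to both would cancel in the comparison. Similar incidence would show that SCRM resembles BCM, not that the risk of SCRM is low.

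At stake is the safety half of the stated aim. The planned test could not carry the conclusion that the Abstract announces, although the adverse-event data to be collected could support a more modest one.

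**Working it through.** **1. Where the 48 comes from.** Inputs from Sample Size: p1 = .895, p2 = .546, difference d = .349, mean rate .7205. The pooled two-proportion formula is

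n = [z(α)·√(2 × .7205 × .2795) + z(β)·√(.895 × .105 + .546 × .454)]² / .349².

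- Two-sided .05, power .90: (1.960 × .6346 + 1.282 × .5847)² / .1218 = 32.6.
- With continuity correction: n/4 × [1 + √(1 + 4/(n·d))]² = 38.1. Then 38.1/0.8 = 47.7, which rounds up to 48. If 38.1 is first rounded up to 39, the result is 39/0.8 = 48.75, so 49.
- One-sided .05: 26.4 uncorrected and 31.9 corrected, or 34 and 40 after rounding up and inflating for dropout.

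The planned size is therefore an efficacy calculation, reproduced in a two-sided, continuity-corrected form. Nothing in it concerns harm.

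**2. Power of the stated safety test.** The article gives no adverse-reaction rates, so the pairs below are assumptions. Method: exact enumeration of two independent binomials, with the Pearson chi-square (no correction) when all expected counts are at least 5, otherwise Fisher, rejecting at P ≤ .05. Both sidedness options are shown because the article states neither. The 38 per arm is 48 × 0.8 = 38.4, rounded down.

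| BCM vs SCRM | 48/arm, two-sided | 48/arm, one-sided | 38/arm, two-sided | 38/arm, one-sided |
|---|---|---|---|---|
| 2% vs 10% | 19% | 30% | 10% | 19% |
| 5% vs 15% | 32% | 41% | 20% | 28% |
| 10% vs 20% | 29% | 37% | 21% | 29% |
| 5% vs 20% | 62% | 70% | 44% | 54% |
| 5% vs 25% | 83% | 88% | 68% | 76% |

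At 48 per arm, two-sided power reaches 80% only when SCRM has about 19% against 1%, 25% against 5%, or 33% against 10%.

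**3. A borderline result.** For 5/48 (SCRM) against 0/48 (BCM), Fisher gives P = .056 two-sided and P = .028 one-sided. The Newcombe 95% interval for the excess is 1.0 to 22.2 percentage points. The verdict of the test turns on an unstated choice of sidedness. The interval shows directly what the data allow. Two-sided significance against 0/48 needs at least 6/48 (12.5%).

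**4. What zero events would show.** The exact upper limit for 0 of n is 1 − .05^(1/n) (one-sided 95%) or 1 − .025^(1/n) (two-sided 95%).

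- n = 48: 6.1% and 7.4%.
- n = 38: 7.6% and 9.3%.

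**5. Rare harm.** The chance of no event in 48 SCRM patients is .99^48 = 62% at a true risk of 1%, and .999^48 = 95% at 0.1%.

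**The case against.** The strongest reply has five parts.

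- **Interpretation.** A reader might infer that the safety conclusion will rest on a non-significant test. The document does not support this. No section equates P >.05 with safety, and the only stated reading of P >.05, given for the superiority test, is cautious. This stands. But that caution is not extended to the safety test.
- **Other safety handling.** Rates and grading of severity and relatedness are planned, so the test is not the whole of the safety evaluation. This also stands. Rates without a measure of precision still put no bound on the risk.
- **Assumed rates.** A reader might infer that the test misses most relevant harms. That needs event rates and a threshold of relevance, and the document gives neither. Large excesses would usually be found if all 48 per arm are retained. The point is therefore limited to moderate excesses.
- **Dropout and sidedness.** The 38 per arm is a worst case: treatment lasts 4 weeks, adverse events are assessed from week 4, and a patient lost late still contributes earlier safety data. One-sided power is higher throughout, but stays between 30% and 41% for the three moderate pairs at 48 per arm.
- **Level of detail.** Confidence intervals for adverse events are commonly left to an analysis plan, which is not shown here. Their absence alone is no finding. The finding is that the stated conclusion outruns the stated test and sample size. No analysis plan can make zero events in 48 patients exclude a 5% risk.

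**Conclusion.** The point holds as a mismatch between claim and method. Chi-square with a Fisher fallback is a valid way to compare incidence, and sizing a trial on efficacy is ordinary. Together, however, they cannot deliver dependable evidence on safety. At 48 per arm, two-sided power is 19% to 32% for the three moderate excesses tried (30% to 41% one-sided) and 83% for 5% versus 25%. These powers rest on assumed rates and full retention. Two parts need no assumed rate: zero events in 48 SCRM patients leaves a risk of up to 6.1% or 7.4%, and a comparison with another rotational thrust cannot show that the risk of SCRM itself is low. The change should be made. It does not bear on the validity of the efficacy comparison.

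**What to change.** In Statistical Analysis, make estimation the main safety analysis:

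- For each arm, the number and proportion of patients with at least one adverse event, with an exact (Clopper-Pearson) 95% interval.
- The SCRM-minus-BCM risk difference, with a Newcombe 95% interval.
- The chi-square or Fisher P value kept as descriptive, with its sidedness stated, and a sentence that non-significance will not be read as evidence that SCRM is safe or as safe as BCM.

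In the Abstract's Conclusions and in Findings and Strengths, limit the safety claim to what those intervals exclude. State that even with no events in 48 SCRM patients only risks above about 6% (one-sided) to 7% (two-sided) are excluded, and that rare serious harms cannot be assessed.

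The cost is a few sentences and a few lines of analysis on data that are being collected anyway, with no added patients or visits. The downside is a more modest safety claim.

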### Ethical Considerations

The study procedures have been reviewed and approved by the Institutional Review Board of Shanghai Baoshan Hospital of Integrated Traditional Chinese and Western Medicine (approval number: 202218), and protocol version 1.0/20221201 is currently active. The full trial has been registered through the Chinese Clinical Trial Registry (identifier: ChiCTR2300068510). Written informed consent will be obtained from all participants before enrolment in the study. Any modifications to the protocol related to deviation of the study aim, study design, patient population, or study procedures will not be implemented until the formal amendment to the protocol is approved by the Institutional Review Board.

## Results

This paper presents an overview of the reasoning and structure of a prospective randomized controlled trial with the objective of investigating the clinical efficacy and safety of SCRM in patients with AJS by assessing improvements in clinical symptoms, neck pain severity, and vertigo severity and evaluating changes in cervical imaging findings. Recruitment was started in March 2023. By the end of May 2024, 76 patients were included in this project. The last follow-up data are predicted to be collected by the end of February 2025. The findings of this study are expected to be submitted for publication in late 2025.

## Discussion

### Findings and Strengths

Globally, manual therapy is considered one of the most crucial clinical therapies for the treatment of cervical spondylosis, and approaches, such as spinal manipulation, chiropractic adjustment, the Mulligan technique, small joint adjustment, and the HVLA technique, are widely used [25-27]. In the context of China, doctors employ diverse techniques in various regions and schools, each possessing distinct technical attributes. In Shanghai, China, the most prevalent technique employed is SCRM, which has demonstrated satisfactory therapeutic outcomes [28]. However, there exists a dearth of evidence-based medical information regarding its efficacy and safety. Consequently, this study aims to examine the effectiveness and safety of SCRM in treating patients with AJS through a prospective randomized controlled trial.

The optimal sample size has been accurately determined based on the findings of our prior research to guarantee sufficient test performance [18]. Subsequently, randomization and blinding procedures will be fully implemented to ensure the study’s classification as a randomized controlled trial. Additionally, a statistical analysis employing a superiority test will be conducted to ascertain that all patients with AJS can receive authentic clinical treatment. As Shi’s Orthopedics and Traumatology Academic School is well known throughout China, with a history of 160 years, it is officially recognized by China’s Health Care Administration, and Shanghai Baoshan Hospital is a branch of Shi’s Orthopedics and Traumatology Academic School. We ensure that the interventions (SCRM and BCM) will be performed by a fixed chief physician with more than 10 years of clinical experience. Moreover, proficient research assistants will be assigned to carry out screening, selection, and follow-up, possessing a comprehensive understanding of the research process for all participants. These measures will greatly contribute to enhancing patient adherence and mitigating the likelihood of attrition in this study. In terms of evaluation metrics, we will employ appropriate standards and develop meticulous professional scales as the primary outcome evaluation indicators to prevent subjective and ambiguous classification assessments, thereby minimizing data distortion and bias. Lastly, we have developed a dedicated electronic information data collection system for this study, guaranteeing the precision, novelty, and security of the data. This study aims to examine the clinical effectiveness and safety of SCRM in patients with AJS by assessing improvements in clinical symptoms, neck pain severity, and vertigo severity and evaluating changes in cervical imaging findings. If successful, this investigation will yield dependable evidence on the efficacy and safety of SCRM in individuals with AJS.

### Limitations

For classification, AJS has been divided into 8 types. For the different types, the SCRM techniques are different, while the BCM techniques are the same. As the incidence rate of AJS is not high, it may be difficult to recruit patients with each type of AJS, who meet the statistical requirements, in a limited time. Therefore, we will not separate the different AJS types, but instead combine them to observe the difference in efficacy between SCRM and BCM. In the future, we will further extend our project timeline and recruit as many subjects as possible for each type of AJS, so that efficacy analysis can be conducted for different types of AJS.

## Abbreviations

AJS: atlantoaxial joint subluxation
BCM: basic cervical manipulation
CT: computed tomography
HVLA: high velocity and low amplitude
NRS: numerical rating scale
SCRM: Shi cervical rotational manipulation
SOP: standard operating procedure
TCM: traditional Chinese medicine
VAS: visual analog scale
VSS-C: Vertigo Symptoms Scale-Chinese Version
